## Appendix A

**Table A1 medicines-06-00013-t0A1:** Phone screening script.

Date:	
Subject Name:	
1. Assuming patient is available for answering questions, ask the following questions:	
2. Are you able to participate in a study which requires the practice of mild daily exercise and **about 11** visits to KU Medical Center over the course of 14 weeks? Specifically there will be 2 visits for assessment prior to and immediately following the study, 9 visits of group exercise sessions during the study. Will this work for you? **YES**—move onto question #3 **NO**—thank them for their time and let them know they are not eligible for this study at this time	
3. Have you been diagnosed with primary (or idiopathic) Parkinson’s disease? **YES**—move onto next question **NO**—thank them for their time and let them know they are not eligible for this study at this time	
4. Are you between the ages of 40 and 75? **YES**—move onto next question **NO**—thank them for their time and let them know they are not eligible for this study at this time	
5. Treatments a) Are you aware of any intentions of changing your medication or dosages over the next three months? **YES** **NO** b) Does your treatment include Deep Brain Stimulation (DBS)? **YES** **NO** **Part a) or Part b): YES**—thank them for their time and let them know they are not eligible for this study at this time **NO**—move onto next question	
6. Have you been diagnosed with any other medical problems (neurological, orthopedic, etc.) that interfere with your ability to do mild body movements and/or follow instructions? **YES**—thank them for their time and let them know they are not eligible for this study at this time **NO**—move onto next question	
7. Are you able to give a simple blood test which includes 30ml (about 1 oz.) of venous blood collection at pre- and post-testing? **YES**—move onto next question **NO**—thank them for their time and let them know they are not eligible for this study at this time	
8. Can you be contacted for participation in the study within two weeks? **YES**—move onto next question **NO**—When will you be available for the study ___________________	
9. What is the phone # and email address to contact you in the next three months? Cell phone # (if available): Email address:

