## 2. Study Design and Aims

### 2.1. Study Design

We designed a double-blind RCT involving 60 individuals with PD (Figure 1). The participants will be randomly assigned to either an experimental (n = 30) or control (n = 30) group. Each group will have group exercise meetings (nine times in total; weekly meeting for first six weeks and then biweekly meetings for next six weeks) throughout the 12 weeks of the intervention period. Participants will be blinded to their group assignments until the end of the study. At baseline, all outcome measures and demographic variables including age, sex, ethnicity, years of education, disease duration, and medications will be collected. After the baseline assessments, participants in both groups will have a 12-week intervention period, including three weeks of training and nine weeks of exercise. The duration of the intervention will be longer than our two previous studies to provide more structured training sessions and longer intervention time [17,18]. During the training period, participants in the experimental group will learn the Qigong exercise, whereas those in the control group will learn the sham Qigong exercise. During the exercise period, participants will continue to practice what they will have learned during the training period. Throughout the 12-week intervention period, all participants will be asked to perform their assigned exercise (Qigong or sham Qigong exercise) twice a day at home, in the morning and evening, attend group meetings (weekly meeting for first six weeks and then biweekly meetings for next six weeks) and keep an exercise diary. The exercise diary includes daily checklists (morning exercise (yes/no), evening exercise (yes/no), and other exercise more than 0.5 h (yes/no)), subjective scales (sleep quality (1–5), fatigue level (0–10), and pain level (0–10)), and participant’s note for any unusual events. Within two weeks after the completion of the 12-week intervention, post-intervention assessments will be conducted, which are the same as the baseline assessments. The assessments will be completed again six months after the end of the intervention period.

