#### 2.4.2. Exclusion Criteria

The study exclusion criteria include (Table 1): (1) Mini Mental State Examination score <24 [31], (2) neurological diseases other than idiopathic PD including other forms of parkinsonism, uncontrolled or significant cardiovascular diseases, orthopedic, balance, or medical problems, (3) prior major head trauma with loss of consciousness, (4) deep brain stimulation, and (5) expected change in PD medications or non-motor symptom medications (e.g., sleep, anxiety, and depression medications) that may affect the results of the proposed outcome measures over the course of the study.

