### 4.3. Serum Biomarkers

Venous blood samples will be collected from participants three times, baseline, post-intervention, and 6-month follow-up. At each timepoint about 30 mL of blood will be collected using the BD vacutainer^®^ blood collection tubes (Becton, Dickinson and Company, Franklin Lakes, NJ, USA; catalog number 367820). Blood draws will be performed by a registered nurse between 9 am and 11 am. After the blood draw, collected samples will be placed at room temperature for approximately 30 minutes for coagulation. Coagulated blood samples will be centrifuged at 1,000 × g at 4 °C for 10 min to separate serum from blood clot and cells. Collected serum will be immediately aliquoted and stored at −80 °C in a freezer until assaying.

When performing the assay, aliquoted samples will be thawed, gently vortexed, and processed to separate any precipitation by centrifugation at 14,000 × g at 4 °C. We will measure the levels of the following biomarkers by enzyme-linked immunosorbent assay (ELISA) using commercially available kits: IL-1β (RayBiotech, Norcross, GA, USA; detection range 3 pg/mL to 1000 pg/mL), IL-6 (RayBiotech, Norcross, GA, USA; detection range 3 pg/mL to 1,000 pg/mL), and TNF-α (ThermoFisher Scientific, Rockford, IL, USA; detection range 15.6 pg/mL to 1,000 pg/mL).

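### The phone screening script describes a 14-week study with two assessments and two blood draws, but the protocol adds a third assessment and draw at about week 38

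*Protocol article*

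**What the plan says.** Section 2.5 makes Table A1 the instrument for the initial phone screening. The script makes four statements or requests that depend on how long the study lasts:

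- Question 2 asks about roughly 11 "visits to KU Medical Center over the course of 14 weeks" and breaks them down: "there will be 2 visits for assessment prior to and immediately following the study, 9 visits of group exercise sessions during the study".
- Question 5a asks "Are you aware of any intentions of changing your medication or dosages over the next three months". A yes ends the call.
- Question 7 asks about 30 mL "of venous blood collection at pre- and post-testing".
- Question 9 asks for a phone number and email address good for the next three months.

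The body of the protocol describes a longer study. Section 2.1 states: "The assessments will be completed again six months after the end of the intervention period". Sections 3.1 and 3.2 repeat the 6-month assessment for both arms, and Figure 1 shows it. Section 4.3 states: "Venous blood samples will be collected from participants three times, baseline, post-intervention, and 6-month follow-up". Section 5.2 puts all three time points in the mixed-design ANOVA. Exclusion criterion (5) in Section 2.4.2 covers expected changes in Parkinson's or non-motor symptom medication "that may affect the results of the proposed outcome measures over the course of the study". Section 3.1 also asks the experimental group to go on with home practice and the diary after week 12.

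**The concern.** This is a contradiction between two parts of the same document. It is not a detail that the article left to a fuller protocol: the script is printed in full, and it gives a duration, a number of assessments and a blood-draw schedule that do not fit the design.

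Two things are at stake.

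- **Eligibility.** If exclusion (5) runs to the end of follow-up, someone who already expects a relevant medication change after month 3 meets it, yet can truthfully answer no to question 5a. Table 1 gives the reason for the criterion: such changes may confound the findings.
- **Retention.** Callers are asked to agree to 14 weeks. The script does not ask whether they can return six months after the intervention or give a third blood sample, and the contact details it collects are sought for a period that ends long before the last visit. The 6-month data feed the stated analysis, so losses there that an accurate script could have prevented are a needless weakness.

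**Working it through.** **Inputs.** Meetings are weekly for six weeks, then every other week for six weeks (Section 2.1). The intervention lasts 12 weeks, the post-intervention assessment falls within two weeks after it, and the follow-up is six months after the end of the intervention (Section 2.1, Figure 1). There are three blood draws (Section 4.3). The script figures are from Table A1. One month is taken as 365.25 / 12 / 7 = 4.35 weeks.

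**Reproducing the script's figures.**

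- Group meetings: 6 + 6/2 = 9.
- Visits: 9 + 2 assessments = 11.
- Duration: 12 + 2 = 14 weeks.

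Both totals come out exactly, but only with the 6-month follow-up left out.

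**With the follow-up included.**

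- Visits: 9 + 3 = 12.
- Duration: 12 + 6 × 4.35 = 38.1 weeks, or 8.8 months. Counting the six months from the latest post-intervention visit at week 14 gives 14 + 26.1 = 40.1 weeks, or 9.2 months.
- Share of the duration that the script mentions: 14 / 38.1 = 37%.

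**Medication window in question 5a.**

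- Three months = 3 × 4.35 = 13.0 weeks.
- Not asked about, if the study runs to the 6-month visit: 38.1 − 13.0 = 25.0 weeks, and 25.0 / 38.1 = 66%.
- Against the latest post-intervention visit: 14 − 13.0 = about 1 week short. This assumes that the intervention starts on the day of the call; any delay widens the gap.

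| Item | Script | Protocol body |
|---|---|---|
| Visits | about 11 | 12 |
| Assessments | 2 | 3 |
| Blood draws | 2 | 3 |
| Duration | 14 weeks | about 38 weeks |
| Medication window | 3 months | course of the study (about 9 months if follow-up counts) |
| Contact period | 3 months | last visit at about 9 months |

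These figures measure how much of the schedule the script covers. They do not measure participants lost, bias or power.

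**The case against.** The strongest reply is that a phone call is not the enrolment gate. Section 2.5 calls it an initial screening and requires physician's permission before participation. Section 2.6 promises detailed information and signed consent, and Figure 1 places consent and baseline before randomisation. The script also asks nothing about Mini Mental State score, Hoehn and Yahr stage, levodopa use or head trauma, so eligibility must be completed elsewhere. All of this stands. It limits the consequence to passing the phone screen. It does not remove the contradiction, and the document describes no later medication question that covers the whole study.

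A second reply is that the document uses the word study loosely. The script itself places the second assessment just after the study, which there can only mean the intervention. On that reading exclusion (5) and question 5a nearly agree. This also stands, and it makes the medication item an ambiguity to settle and not a proven misapplied exclusion. Question 5a is also broader in one respect: it asks about any medication, while exclusion (5) is limited to changes that may affect the outcomes.

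A third reply is that the word about before 11 allows for a twelfth visit. That may be so for the count, but 14 weeks, two assessments and blood only at pre- and post-testing leave no room for a visit near week 38.

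A reader might also infer more than the documents support:

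- **That such callers are randomised and then withdrawn.** The later steps may stop them, and withdrawal criterion (4) in Section 2.4.3 applies only to major changes. A planned change need not be major.
- **That the ANOVA discards the post-intervention data of anyone who misses the 6-month visit.** Section 5.2 states no complete-case rule, and missing-data handling may be set out in an analysis plan that is not shown.
- **That the plan budgets for losing 9 of 30 per arm.** Section 5.1 uses the 30% dropout to go from 14 to 14 / 0.70 = 20 per arm. It justifies 30 by the secondary hypotheses. Even 30% of 30 lost would leave 21 per arm, more than the 14 calculated for the primary outcome.

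**Conclusion.** The contradiction is established for the number of visits, assessments and blood draws and for the duration: 11 against 12, two against three, two against three, and 14 against about 38 weeks. The contact period is likewise shorter than the follow-up. For the medication window, the wording of the script and that of exclusion (5) differ. The gap is about 25 weeks if the study includes follow-up, and close to nil if the study means the intervention alone.

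The supported consequence is that a caller who cannot attend at six months, or who expects a relevant medication change after month 3, can pass the phone screen. The number of such callers is unknown, because the documents give no figure. The exposure is mainly at the 6-month time point. The post-intervention comparison is much less affected, since three months spans the 12-week intervention. No loss of power for the primary outcome is shown. The correction is still worth making: it costs very little, and it protects a time point that the analysis uses.

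**What to change.** Amend Table A1:

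- **Question 2:** 12 visits over about 9 months, naming the 6-month assessment.
- **Question 7:** three blood draws, at baseline, post-intervention and 6 months.
- **Question 9:** contact details for the period up to the 6-month visit.
- **Question 5a:** reconcile its window with exclusion (5), so that both name the same period. The study team decides which period applies, and should say whether the course of the study includes follow-up.

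The cost is a revised script and a notification to the Institutional Review Board. A few more callers will decline or be screened out. Section 2.5 expects about two thirds of some 1,600 patients seen each year to qualify (1,600 × 2/3 = about 1,067), a large pool against a target of 60. The design, outcomes and analysis do not change.
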